The intervention will begin in year 2. We will distribute guidelines and definitions concerning ABU and CAUTI at both sites in the form of a diagnostic algorithm. Guideline distribution to providers will continue at appropriate intervals at both sites for the ensuing two years. During the second year, we will provide individualized audit and feedback at the intervention site. The research team will review episodes of bacteriuria and the management implemented by the provider who ordered the urine culture. Research personnel will then visit the provider to discuss whether his or her behavior was or was not in compliance with ABU guidelines. Unit-level feedback will also be given by the research assistant on a monthly basis by presenting the unit's results in graphical form. The unit in this case will be the five hospital wards for the long-term care patients and the eight internal medicine teams for the medicine wards. At the control site, algorithm distribution alone will occur during the second year. During the second year, we will also evaluate the effect of the intervention on the barriers to guidelines implementation in terms of awareness, familiarity, acceptance, and outcome expectancy through pre/post surveys completed by healthcare providers at the intervention site. Exit (qualitative) interviews with study participants will also address potential barriers to implementation of our intervention protocol.

During the third year of the study, the individualized visits to providers will cease, but unit-level feedback will continue over the course of the third year at the intervention site. During this year, the surveys will be administered at the control site in addition to the intervention site so that we can assess the effect that the surveys alone have on prescribing behavior and on responses to survey questions. The purpose of the third year is to continue to measure elements of the study, as well as to evaluate issues of sustainability and the minimal intervention elements needed for dissemination.

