### Setting and participants

#### Setting

The intervention site and the control sites were chosen because they are alike in terms of ward organization, patient population, infection-control software, and clinician and medical resident involvement in patient care. We also studied the organizational context of the proposed intervention site (MEDVAMC) and control site (STVHCS) using the results of the VA Clinical Practice Organizational Survey (CPOS), Chief of Staff Module, with specific focus on responses to survey elements concerning support for guideline adherence and implementation of quality improvement measures [27]. Overall, the two sites are similar in several key elements relevant to our project. In particular, audit and feedback is not used extensively at either site and is primarily applied to clinicians' laboratory test ordering. Both sites rely on designated site champions to implement clinical guidelines or performance measures, although finding someone willing to take on this role was difficult at one of these sites because of time constraints. The leaders at both sites are strongly committed to continual improvement.

We believe that a hospital-wide intervention will be necessary (as opposed to intervening at the ward level) because medical residents travel throughout the hospital via consult services and thus, may potentially serve to diffuse knowledge throughout the facility. Hospital units at the intervention site with the highest rates of guideline-noncompliant behavior were identified, including the five general medicine wards and the five extended-care units, where 36.1% of patients received inappropriate treatment. The corresponding units at the control site have been selected for our study (three medicine wards and two extended-care wards). The intervention and control facilities are in different Veterans Integrated Service Networks, or VISNs, which is advantageous for study purposes. For the STVHCS to be a true control, healthcare providers should not overlap or have significant work-related communication with the intervention facility. Also, performing the study in two different VISNs will ultimately facilitate diffusion of the study intervention.

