#### Healthcare providers targeted in the intervention

The audit and feedback intervention will be applied to the healthcare providers who make the decision to treat CAUTI. The healthcare provider who makes the decision to order a urine culture and to prescribe antibiotics for a positive urine culture differs depending on hospital unit. In the internal-medicine wards, this decision is made by internal-medicine residents, who are usually either interns or second-year residents (postgraduate year 1 or 2). Approximately 170 medical residents rotate through the intervention site medicine wards per year. The extended-care units are staffed by nurse practitioners and physician assistants, with supervision provided by VA staff physicians trained in geriatrics. Therefore, in the extended-care ward, the intervention will target the nurse practitioners, physician assistants, and staff physicians, currently 17 individuals.

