### Analysis

#### Analysis plan and sample size for objective 1

##### Independent variables for objective 1

For the variables in objective 1, it is important to understand that the intervention is applied to the healthcare providers, but the unit of analysis for the outcomes is episodes of bacteriuria occurring in catheterized inpatients (Table 3). We will account for the correlation that may exist among patients treated by the same healthcare provider in our regression models. The independent variables include age and gender of the patient, duration of catheter use, catheter type, hospital ward and service, types and quantities of organisms found in the urine, number of white blood cells (WBCs) in urine, number of WBCs in the serum, and highest temperature in 24 hours around the time of urine specimen collection.

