##### Dependent variables for objective 1a--inappropriate treatment

The main outcome of interest for this objective is the number of cases of ABU that are managed inappropriately out of all episodes of bacteriuria. This determination will be made by applying the diagnostic algorithm. The dependent variable to be used in the analytic models will be whether or not each episode of bacteriuria is managed inappropriately. The unit for analysis will be episodes of bacteriuria.

A secondary outcome will be the number of days that antibiotics are given to treat ABU. We will determine the reason for treatment of bacteriuria (if stated in the medical record), antibiotics given, and duration of treatment. As a safety issue, we will monitor outcomes of bacteriuria at both sites for 30 days following the episode. These outcomes will include any side effects of the antibiotics given, isolation of an organism resistant to the antibiotics given, or *Clostridium difficile *colitis. We will also monitor for any complications that may develop from bacteriuria, such as symptomatic UTI, pyelonephritis, and urosepsis.

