##### Estimated sample size for objective 1b--inappropriate screening

We do not have estimates of the percentage of catheterized patients who are screened for ABU. We have based our estimates of the sample size on detecting a reduction in the intervention group of 25% in the percentage of catheterized patients who are screened for ABU. Based on estimates of the number of catheterized patients at Houston and San Antonio in a one-year time period (1,867 and 1,512, respectively), we will have 80% power to detect a 25% reduction in percentage of patients screened, even if the percentage of screened patients is as low as 10%.

#### Analyses for objective 1

For the analysis of inappropriate treatment, we will test for differences in the proportion of inappropriately treated episodes of bacteriuria between intervention and control sites using a hierarchical regression approach. Episodes will be nested within patients and patients nested within provider. Independent variables will be those described above. A significant value for the parameter estimate for the intervention will indicate that the audit feedback group differed from the control group.

For the analysis of inappropriate screening, we will conduct a logistical regression analysis in which the dependent variable will be whether or not the catheterized patient received screening for ABU. Hierarchical models will allow nesting of patients within provider. An indicator variable for the intervention effect will be used to determine differences between the audit feedback and control groups. Independent variables will include variables to indicate the unit in which the patient was hospitalized in addition to patient-related characteristics. A similar logistical analysis will be run for the secondary outcome of whether or not the hospitalized patient had a urinary catheter. For both the primary and secondary outcomes, the number of cultures per 100 device-days and the number of device-days per 100 bed-days will be compared among the units using analysis of covariance.

For the secondary outcome of days of inappropriate antibiotic use, we will first examine the distribution of the number of days that antibiotics were given. If the distribution is not normally distributed, we will consider appropriate transformations. In addition, we may consider use of hierarchical Poisson regression models.

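### Objective 1a: nesting patients strictly within one provider does not fit a provider who is fixed per episode, so a patient's repeat episodes under different providers are modelled as independent or misattributed

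*Protocol article*

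**What the plan says.** Under Analyses for objective 1, the protocol article tests the difference between sites in the proportion of episodes treated inappropriately, using a hierarchical regression: "Episodes will be nested within patients and patients nested within provider". The analytic unit is the episode: "The unit for analysis will be episodes of bacteriuria" (Dependent variables for objective 1a). The section on independent variables names one source of correlation: "We will account for the correlation that may exist among patients treated by the same healthcare provider in our regression models".

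Elsewhere the article describes how providers and episodes meet:

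- Study timeline: "The research team will review episodes of bacteriuria and the management implemented by the provider who ordered the urine culture". The provider is identified for each culture.
- Healthcare providers targeted in the intervention: "Approximately 170 medical residents rotate through the intervention site medicine wards per year". In extended care, "the intervention will target the nurse practitioners, physician assistants, and staff physicians, currently 17 individuals".
- Study timeline: surveillance runs at both sites for all three years.

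The article gives no rule for a patient whose episodes belong to different providers.

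**The concern.** A three-level hierarchy is valid only if each lower unit belongs to exactly one higher unit. Episodes belong to one patient, so the first step holds. Patients need not belong to one provider: the provider is a property of the episode, residents change over the year, and three years leave time for readmission or a further episode. By including a level for episodes within patients, the plan itself expects some patients to contribute more than one.

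If a patient has one episode under provider A and another under provider B, the stated structure allows two codings. Either the patient is coded separately inside A and inside B, and the two episodes share no random effect. Or the patient is assigned to one provider, and the other episode is charged to someone who did not manage it. The first loses the patient's own correlation; the second distorts the provider effect. At stake are the standard error and type I error of the main 1a comparison.

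**Working it through.** **The plan's own figure.** Inputs from Estimated sample size for objective 1a: 36% against 25%, two-sided α = 0.05, power 80%, h = 1.287 − 1.047 = 0.240. The arcsine formula gives n = 2(1.960 + 0.842)²/0.240² ≈ 273 episodes per site. A continuity-corrected two-proportion formula gives 292. The stated 300 is close to the latter and a cautious round-up of the former (power at 300 is about 83.6%). It contains no clustering term, so the nesting question does not change it. The question concerns the analysis.

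**What each structure implies.** Let σ²ₚ be the patient variance, and take two episodes of one patient under providers A and B.

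- Strictly nested (patient coded inside provider): modelled covariance = 0.
- Crossed patient and provider effects: modelled covariance = σ²ₚ.
- Both episodes under the same provider: the two structures agree, so nothing is lost.

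**Direction.** A patient's episodes will in practice lie at one site, so in a between-site contrast they enter with the same sign. Var(a + b) = Var(a) + Var(b) + 2Cov(a, b), and omitting a positive covariance understates the variance. In a pre/post-by-site contrast, a year 1 and a year 2 episode of one patient enter with opposite signs. Var(a − b) = Var(a) + Var(b) − 2Cov(a, b), and the omission overstates the variance.

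**Size for the between-site contrast.** The article gives none of the following inputs, so all are assumptions:

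- share of episodes from patients with repeats, s = 0.2 to 0.5;
- episodes per such patient, m = 2 to 4;
- within-patient correlation, ρ = 0.2 to 0.5;
- share d of same-patient pairs that fall under different providers.

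Inflation = [1 + s(m − 1)ρ] / [1 + s(m − 1)ρ(1 − d)]. True size = 2[1 − Φ(1.96/√inflation)].

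| Case | Inflation | True size |
|---|---|---|
| Low, d = 0.5 | 1.04/1.02 = 1.02 | 5.2% |
| Low, d = 1 | 1 + 0.2 × 1 × 0.2 = 1.04 | 5.5% |
| High, d = 0.5 | 1.75/1.375 = 1.27 | 8.2% |
| High, d = 1 | 1 + 0.5 × 3 × 0.5 = 1.75 | 13.8% |
| Any, d = 0 | 1.00 | 5.0% |

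**Cross-check by another route.** In a linear approximation to the mixed model, the true covariance was crossed and the working covariance nested, with 300 episodes per site, a provider variance share of 0.05 and 17 or 170 providers per site. Every patient was given 2 or 3 episodes, the patient variance share was 0.1 to 0.5, and 50% or 100% of repeats were redrawn to a random provider. The true variance of the site contrast exceeded the reported one by a factor of 1.03 to 1.92 (true size 5.3% to 15.7%). The upper end is above 1.75 because every patient recurs in that set-up. A middle case (2 episodes, patient share 0.3, all repeats redrawn, 170 providers) gives 1.28 and 8.3%.

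**The case against.** **Recurrence is not documented.** The article does not say how many patients recur or under whom. The background figure that nearly all patients catheterised for 30 days or longer have bacteriuria might be read as evidence of many repeats. It is a prevalence, and a study episode also needs a culture to have been sent. It gives no recurrence rate and is not relied on here. This objection stands, and it makes the size conditional.

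**Repeats and rotation may sit in different wards.** Long-stay patients, a plausible source of repeats, are in extended care with 17 staff, while the roughly 170 residents rotate through the medicine wards. Repeats that stay with one provider are handled correctly. This stands and could bring the effect close to nil. A reader might also take the remark that "medical residents travel throughout the hospital via consult services" as evidence about attribution; in the article it concerns diffusion of knowledge.

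**Covariates would absorb some of the correlation.** Catheter type and duration, ward, organisms, white-cell counts and temperature are in the model. That is fair, and favours the lower part of the range.

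**The direction depends on the contrast.** The design is described as controlled pre/post, and for that contrast the sign can reverse. This stands as a qualification. The test worded under Analyses for objective 1 is the site difference, to which the stated direction applies.

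**The same fault might be inferred for objective 1b**, where "Hierarchical models will allow nesting of patients within provider". The article does not support that. The 1b regression has one yes/no outcome per catheterised patient, so there are no repeat episodes whose correlation is lost. Nor could an attribution rule based on the ordering provider work there, because an unscreened patient has none.

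**Coding of random effects is often left to an analysis plan.** That would excuse silence. Here the article names the structure, and the structure named does not match its own description of providers.

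**Conclusion.** The point holds for objective 1a. Strict nesting of patients within provider is inconsistent with a provider identified per culture, rotating residents and three years of surveillance. Where repeats change provider and are coded as separate patients, the between-site standard error is too small: inflation of roughly 1.02 to 1.75 and a true size of about 5.2% to 14% under the assumed recurrence, correlation and share of changes. The effect is negligible if few repeats change provider.

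A stronger reading, that the 1a test is certainly and materially anti-conservative, is not supported. The inputs that decide the size are absent from the article, and the direction is not assured for a pre/post-by-site contrast. The structure is worth correcting because it is wrong in kind and cheap to put right.

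**What to change.** For objective 1a, replace the strict hierarchy by a cross-classified model: one random effect for patient and one for provider, crossed, with patient identifiers unique across the whole study so that a patient seen under two providers remains one patient. State a single rule, the same at both sites, that attributes each episode to one provider. Leave the 1b model outside this change.

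The cost is small: slightly wider intervals where repeats change provider, longer fitting, and recording each episode's provider at the control site as well as the intervention site. The provider-level model already stated needs that last item in any case. If repeats under different providers turn out to be rare, the crossed model gives nearly the same answer as the nested one.

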## Background

Urinary tract infection (UTI) is the single most common hospital-acquired infection, and many cases of nosocomial UTI are associated with an indwelling urinary catheter [1,2]. Urinary catheters bypass normal host defenses, and bacteriuria develops at the rate of approximately 5% per day; [3] nearly all individuals (98%) who are catheterized for 30 days or longer will have bacteriuria caused by one or more species of potentially pathogenic bacteria [4,5]. Furthermore, organisms causing catheter-associated urinary tract infection (CAUTI) are frequently resistant to one or more antibiotics [6,7]. In addition to these concerns regarding quality of care, annual incremental costs attributed to nosocomial CAUTI in 2002 were estimated to exceed $451 million [8]. Finally, since public reporting of nosocomial infections has become mandated in more than 30 states, [9] hospitals have strong incentive to reduce their rates of hospital-acquired CAUTI.

An important distinction exists between CAUTI and asymptomatic bacteriuria (ABU). CAUTI, as defined by the US Centers for Disease Control (CDC) and the National Healthcare Safety Network, involves symptoms (fever, urgency, frequency, dysuria, or suprapubic tenderness), in addition to microorganisms in the urine [10]. CAUTI requires antimicrobial treatment to relieve symptoms, while patients with ABU are, by definition, asymptomatic. Treatment of ABU in patients with an indwelling catheter does not improve morbidity or mortality, nor does it decrease the incidence of symptomatic CAUTI [11]. Use of antimicrobial agents to prevent or to treat catheter-associated ABU does lead to emergence of resistant flora, however [12]. Accordingly, evidence-based guidelines concerning ABU have stated that it is inappropriate to screen for or to treat ABU associated with the presence of a urinary catheter, with the exceptions of pregnant women and persons undergoing invasive urologic procedures [11,13]. The CDC campaign to prevent antimicrobial resistance in hospitalized patients likewise instructs clinicians to "treat infection, not colonization." [14] Unfortunately, a significant translation gap between evidence-based guidelines concerning management of ABU and clinical practice has been observed throughout the world [15,16]. Overtreatment of ABU is a quality, safety, and cost issue, particularly as unnecessary antibiotics lead to emergence of resistant pathogens [14,17].

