## Methods

### Study design

The study uses a controlled pre/post design to test an intervention using audit and feedback of healthcare providers to improve their compliance with ABU guidelines. The intervention and the control sites are two different VA hospitals.

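### As written, the objective 1 models do not identify the intervention effect: ward indicators absorb the site contrast, and no period or site-by-period term is stated

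*Protocol article*

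**What the plan says.** The Study design section states: "The study uses a controlled pre/post design to test an intervention". Table 1 and the Study timeline give both hospitals a baseline surveillance year, with audit and feedback at the intervention hospital only from year 2.

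The Analyses for objective 1 section does not carry this structure into the models.

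- **Inappropriate treatment (1a), ranked first in Table 3.** A hierarchical regression compares the proportion of inappropriately treated episodes between the two sites. Episodes are nested in patients and patients in providers. The conclusion rests on the significance of the intervention parameter. The covariates are those of the section Independent variables for objective 1: "The independent variables include age and gender of the patient, duration of catheter use, catheter type, hospital ward and service", followed by organism and white-cell measures and "highest temperature in 24 hours around the time of urine specimen collection".
- **Inappropriate screening (1b).** A logistic model, with patients nested in providers, has an indicator for audit-feedback versus control. It then adds: "Independent variables will include variables to indicate the unit in which the patient was hospitalized in addition to patient-related characteristics".

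Neither model is given a period term or a site-by-period term.

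The Setting section lists the wards: "the five general medicine wards and the five extended-care units" at the intervention hospital and "three medicine wards and two extended-care wards" at the control hospital.

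**The concern.** A ward sits in one hospital, so knowing the ward means knowing the site. A model with an indicator for every ward has no information left from which to estimate a site difference. Yet the site difference is the only intervention contrast that the analysis section describes, and both objective 1 conclusions depend on it.

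The software will not necessarily stop. It may drop the intervention term, or it may drop a further ward and print a coefficient that looks like an intervention effect but is not one.

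The omission also affects what is being estimated. A controlled pre/post study asks whether the change over time differs between sites. A bare group contrast does not ask that, even when it can be computed.

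**Working it through.** **1. The plan's own figure.** The sample size section for 1a gives 300 episodes per site for 36% v 25%, two-sided α = 0.05, power 80%, by the arcsine method.

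- h = 2·arcsin√0.36 − 2·arcsin√0.25 = 1.287 − 1.047 = 0.240, as printed.
- n = 2·[(1.960 + 0.842)/0.240]² ≈ 273 per site. With 300 per site the power is 83.6%.

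The figure is reproduced and slightly conservative. It confirms that the study was sized for a site-versus-site difference with no baseline period.

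**2. Rank of the model as written.** Inputs from Setting: 5 + 5 = 10 intervention wards and 3 + 2 = 5 control wards, 15 in all. Let W1 to W10 be the intervention ward indicators, W11 to W15 the control ward indicators, and G the group indicator. Then

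G = W1 + W2 + … + W10, exactly.

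| Fixed effects | Columns | Rank |
|---|---|---|
| 15 wards + group (year 2 only, or all three years) | 16 | 15 |
| 15 wards + post-period + site × post-period | 17 | 17 |
| Intercept + service + group, no ward | 3 | 3 |

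The first row has no unique solution for the group term, and more data do not help.

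**3. What software would print.** Keep an intercept and the group term, and drop one ward per site, say ward a (intervention) and ward b (control). Apart from other covariates, the group coefficient is then the outcome level in ward a minus that in ward b. It is a contrast of two arbitrary wards and changes when the dropped wards change.

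**4. The alternative coding.** Suppose the indicator is 1 only at the intervention site after year 1, all wards are kept and there is no period term. The model has 15 + 1 = 16 columns and rank 16, so it can be estimated. But the indicator is 0 throughout in every control ward, so apart from helping to estimate covariate slopes those wards contribute nothing to the coefficient. In a numerical check (intervention wards falling by 0.3), the coefficient stayed at −0.3 whether control wards changed by 0, −0.3 or +1 over the same time. With a period term added, the three answers were 0 − 0.3 = −0.3, −0.3 + 0.3 = 0 and −0.3 − 1 = −1.3, as a controlled design requires.

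**5. Precision of the corrected estimate.** Assume 300 independent episodes per site per period, 36% in three cells and 25% in the intervention site's post-period, on the risk-difference scale.

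- Site contrast: SE = √[(0.2304 + 0.1875)/300] = 0.0373.
- Difference in differences: SE = √[(3 × 0.2304 + 0.1875)/300] = 0.0541, which is 1.45 times as large.
- Power for a difference of 0.11: Φ(0.11/0.0541 − 1.96) ≈ 53%, against about 84% for the site contrast.
- For 80% power: (1.960 + 0.842)² × 0.8787/0.11² ≈ 570 episodes per site per period.

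**The case against.** The strongest reply is that the aliasing is conditional. The design is declared as controlled pre/post, so an informed reader may supply the site-by-period term. With that term and a period effect, every ward indicator can stay. On this view the covariate list is not at fault, and the coding of ward is a detail for an analysis plan that is not shown.

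Part of this stands. The defect lies in the unstated period structure rather than in listing ward as such, and for 1a the text lists ward without saying that it enters as fixed indicators. The reply does not rescue the text, because the analysis section does state a contrast, group against group, and the sample size section sizes that same contrast. A random ward intercept would make the group term estimable, but the term would remain a between-site comparison with no baseline correction. The nesting levels named are also only patient and provider.

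Stronger readings are tempting, and the documents do not support them:

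- *The quoted unit indicators show that the primary model fails.* That sentence belongs to the screening model. For 1a the support is the covariate list.
- *Temperature defines the outcome.* The Background says that CAUTI "involves symptoms (fever, urgency, frequency, dysuria, or suprapubic tenderness), in addition to microorganisms in the urine", so fever is one of five symptoms. The study classifies episodes by its own algorithm, which is not reproduced, and the outcome also depends on what the provider did. Separation of the data on temperature cannot be shown, since no temperature distribution is given.
- *Catheter duration is a mediator.* The article says that the intervention may lead to catheter removal, but not over what window duration is counted. Mediation is possible, not demonstrated.
- *Some covariates are known only for cultured patients.* In 1a every analysed episode comes from a culture. Any selection concerns the denominator, and dropping covariates would not cure it.
- *The covariate list should be cut to a few baseline variables.* That is a preference. Two non-randomised sites can justify broad case-mix adjustment.

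**Conclusion.** The point holds in this form: as written, neither objective 1 model identifies the effect of the intervention. Under fixed ward indicators the stated group term is aliased (rank 15 of 16). Under exposure coding without a period term, the result is an uncontrolled before/after comparison at one hospital. With period and site-by-period terms the problem disappears (rank 17 of 17).

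The rank result assumes fixed ward or unit indicators, which the text states for 1b and leaves open for 1a. The need for a period structure does not depend on that assumption. Over-adjustment for temperature and catheter duration is a risk to examine, not an established error.

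**What to change.** In Analyses for objective 1, define the intervention effect for both 1a and 1b as the site-by-period interaction, with period main effects, using the baseline year already collected at both hospitals. Keep the ward indicators, which then absorb the site main effect. Individual feedback stops after year 2, so years 2 and 3 can each have their own period and interaction term: 15 + 2 + 2 = 19 columns, full rank. State that the conclusion rests on the interaction.

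As a sensitivity analysis, report the primary effect with and without temperature and catheter duration, and state the window over which duration is counted.

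No new data collection is needed, and the article describes the study as still in its baseline year. The cost is precision: under the assumptions in the working, the standard error rises by about 45%, and roughly 570 rather than 300 episodes per site per period would give 80% power. The article reports over 3,000 catheter-associated discharges in one year across both sites but no count of bacteriuria episodes, so whether that number is reached cannot be judged from it. The baseline year will show. The 570 makes no allowance for clustering by provider or ward.
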